## 2 INTRODUCTION

Healthcare workers have a high incidence of stress-related disorders, including burnout, insomnia, and depression, with burnout rates around 50% among physicians in internal medicine, emergency medicine, and other highly impacted specialties (Medscape, 2020; National Academy of Medicine, 2019). With the emergence of COVID-19 infection, stress levels in healthcare workers have markedly increased (Hoffman, 2020). Not only are the patients being treated more ill, but healthcare workers are feeling vulnerable to contracting the infection themselves. In addition, when they return home, they are concerned that they may be carrying the infection to their families—all of which is contributing to their increased burden of stress.

Hospitals and medical centers around the US, in their missions of healing, are seeking additional means, particularly non-pharmacologic means, for helping staff. The technique of Transcendental Meditation is a well-documented approach for stress-reduction and promotion of resilience, which has been shown to be effective in a healthcare setting. We propose offering this unique technique to a population of healthcare workers at three Miami-area hospitals – Baptist Health South Florida Hospital, Mercy Miami Hospital, and Encompass Health Rehabilitation Hospital of Miami and studying the benefits using validated mental health and well-being scales.

Healthcare provider (HCP) burnout is a national crisis, negatively affecting patient care, and contributing to provider shortages—at a cost of an estimated 4.5 billion dollars annually (West et al., 2018; Han et al., 2019). Burnout is a state characterized by emotional exhaustion, depersonalization, and decreased sense of personal accomplishment, typically present in those under constant pressure (Maslach et al., 1998; WHO, 2019). Low resilience, defined as the inability to cope with daily stressors and overcome challenges, is a critical determinant of burnout (Yilmaz, 2017). Frontline healthcare providers, including emergency medicine and critical care (ICU) personnel, exhibit particularly high levels of burnout and dissatisfaction (Medscape, 2020; Embriaco et al., 2007). More hospitals are pro-actively supporting provider wellness, as evidenced by the availability of coaching, behavioral and wellness programs (Shanafelt, 2009).

This proposal aims to optimize and evaluate HCP wellness and performance at three Miami-based hospitals – Baptist Health South Florida Hospital, Mercy Miami Hospital, and Encompass Health Rehabilitation Hospital of Miami – through an evidence-based stress reduction program, Transcendental Meditation. It is particularly timely due to the enormous pressure and stress that frontline HCPs face due to the current COVID-19 pandemic. Funding for the program and the analysis of the benefits will be

provided through a combination of grants from local Miami donors and matching funds from the David Lynch Foundation, a 501(c)3 nonprofit organization.

Background: Transcendental Meditation (TM) is a mind-body program that allows the practitioner to experience progressively quieter, less excited states of mental activity, with the growing experience of restful alertness in mind and body (Roth, 2018). It has been found to be effective in reducing adverse mental health outcomes, including burnout, emotional exhaustion, depression, anxiety, insomnia, and trauma symptom severity, and in increasing resilience and other positive factors (Jayadeevapa et al., 2007; Elder et al., 2015; Valosek et al., 2018; Nidich et al., 2018). The following summarizes some of the main findings on TM in the area of mental health for health care providers as well as other at risk populations.

A randomized controlled trial (RCT) with 40 academic physicians at University of Loyola Stritch Medical School, Chicago, showed practice of TM decreased burnout, depression, and sleep problems over a 4-month intervention period. Compliance with daily practice of meditation was good, with 75% of the physicians meditating at least once day at 4-month posttest (Loiselle et al., manuscript under preparation).

An uncontrolled 3-month pilot study of emergency medicine faculty physicians and residents at Weill Cornell Medical Center who were instructed in the TM technique found significant improvements in physician burnout, post-traumatic stress symptoms, and sleep disturbance (Weill Cornell Medical College, 2019). TM practice compliance was good, with those practicing twice a day on average (for about 15-20 minutes each session), showing better improvement on study outcomes at 3-month posttest than those practicing once a day. In an uncontrolled study with family caregivers, significant improvement was observed in symptoms of depression, anxiety, anger/hostility, fatigue, and optimism as well as other quality of life factors (Nidich et al., 2015).

A randomized controlled study with Transcendental Meditation in special education teachers in a high stress environment indicated significant decreases in burnout, depression, and perceived stress over a 4-month intervention period (Elder et al., 2015). A follow-up RCT showed corroboration of the findings on burnout as well as a significant increase in resilience (Valosek, Wendt, et. al., manuscript under review). Further research on TM has shown increased resilience across various groups (Bandy et al. manuscript under preparation; Wendt et al., 2015) as well as improvement in other social-emotional health factors such as self-actualization, emotional intelligence, and positive coping behavior (Valosek et al., 2018; Nidich et al., 2009).

A recent phase II clinical trial published in *Lancet Psychiatry* and funded by the U.S. Department of Defense indicated efficacy of TM to reduce PTSD symptoms, depression, and total mood disturbance, and improve overall quality of life in veterans with documented PTSD. TM was found to be non-inferior to the “gold standard” trauma-focused prolonged exposure therapy (PE), and superior to an active PTSD health education (HE) control group on all study outcomes. In the TM group 60% of participants exhibited clinically significant reductions in PTSD symptoms compared to 43% for PE and 32% for HE (Nidich, Mills et al., 2018). A recent RCT at Northwell Health, New York, with military veterans diagnosed with PTSD, found that 50% in the TM group had lost their PTSD diagnosis at 3-month posttest compared to 10% in the treatment-as-usual group (Bellehsen et al., submitted for publication).

Research indicates that Transcendental Meditation (TM) may significantly decrease anxiety and depression in both healthy adults and chronically ill patient populations. In a randomized controlled study with heart failure patients conducted at the University of Pennsylvania Medical School, patients practicing TM showed significant decrease in depression compared to a control group participating in a health education intervention over six months (Jayadeevapa et al., 2007). HIV and breast cancer patients

also showed improved mental health and quality of life through TM (Chhatre et al., 2013; Nidich, Fields et al., 2009). A meta-analysis on anxiety reporting on 1295 subjects found that TM significantly decreases anxiety, with a large effect size. Compared to other meta-analyses, TM was observed to exhibit a larger effect size than other forms of meditation (Orme-Johnson & Barnes, 2013).

Prior research on TM funded by the National Institutes of Health over the past several decades has further shown positive effects on cardiovascular disease (CVD) risk factors and clinical events (see e.g., Walton et al., 2004; Schneider et al., 2005; Anderson et al., 2008; Schneider et al., 2012).

### **3 OBJECTIVES**

#### **3.1 Primary and Secondary Objectives**

##### Primary Endpoints:

1. Burnout: The Maslach Burnout Inventory (MBI-HSS) for Medical Personnel will be used to measure participant burnout [15]. The MBI-HSS is a 22-item inventory with a seven-point response scale, measuring emotional exhaustion (9 items), depersonalization (5 items), and personal accomplishment (8 items). Cronbach's alphas range from .76 to .90 (Iwanicki et al., 1981).
2. Insomnia: Insomnia Severity Index (ISI). The ISI is a 7-item scale, measuring severity of sleep problems. The ISI has satisfactory internal reliability (Cronbach's alpha=.74) (Bastien et al., 2001).
3. Symptom: Brief Symptom Inventory 18 (BSI 18). The BSI 18 is a 5-point rating scale used to gather patient-reported data to measure psychological distress and psychiatric disorders in medical and community populations. (Derogatis et al, 2001).
4. Well-Being: Warwick Edinburgh Mental Well Being Scale (WEMWBS) is a 14-item scale with 5 response categories, summed to provide a single score. The items are all worded positively and cover both feeling and functioning aspects of mental wellbeing, thereby making the concept more accessible. (Tennant et al, 2006).

#### **3.2 Study Overview**

Sixty-five healthcare providers and hospital administrators (HCPs) affiliated with the three participating Miami hospitals will be instructed in Transcendental Meditation Technique as follows: 25 at Baptist Health South Florida Hospital, 25 at Mercy Miami Hospital, and 15 at Encompass Health Rehabilitation Hospital of Miami. A control group of similar numbers of HCPs at each institution will also be recruited, and matched to the extent possible for gender, age, type of HCP (doctor, nurse, etc.), and work schedule (e.g., days, nights, etc.). Study outcomes will be assessed at baseline, 2 weeks, 1 month, and 3 months posttest, with change in burnout as the primary outcome. The total duration of the study period will be 3 months.

## **4 STUDY POPULATION**

### **4.1 Inclusion Criteria**

Subjects who meet all of the following criteria are eligible for this study:

- 1) Fulltime healthcare providers, medical doctors, physician assistants, nurses or other HCPs involved in active patient care or administration of patient care (Hospital Administration).
- 2) 18 years or older.
- 3) Have treated COVID-19 patients or working at locations where COVID-19 patients are being treated.
- 4) Willing and able to complete both baseline and post-testing as noted above.
- 5) If being treated with psychoactive medications, the maintenance of a stable regimen for at least two months before enrollment.
- 6) In the non-control group, willing and able to dedicate the time to learning the Transcendental Meditation technique and practice it twice daily for approximately 20 minutes.

### **4.2 Exclusion Criteria**

Subjects who meet any of the following criteria are not eligible for this study:

- 1) Already instructed in the Transcendental Meditation technique.
- 2) Currently unstable psychiatric symptoms as demonstrated by self-report, medical chart, or psychiatric hospitalizations in the past six months.

### **4.3 Withdrawal and Replacement of Subjects**

Subjects who withdraw consent must be withdrawn from the study. No justification for such a decision is required. Subjects must be withdrawn from the study if the investigator considers it in the best interest of the subject that he/she be withdrawn. Subject must notify the principal investigator in writing at the time of their decision. The reasons for withdrawal must be recorded, if available, on the case report form (CRF) and in the subject's medical records.

### **4.4 Subjects Identification**

All subjects enrolled must be identifiable throughout the study. The research study staff will maintain a personal list of subject numbers and subject names to enable records to be found at a later date.

Subjects will receive a subject number as detailed in a separate document located in the investigator's file. Subjects who terminate their study participation for any reason after signing the consent form, regardless of whether study medication was taken or not, will retain their subject identification number. In that case, the next subject identification number and bottle in the sequence are to be used. The following subject is given the next subject identification number. Screen failures will not be assigned a subject identification number. Screen failures are not to interrupt the subject identification schema for the enrolled subjects.

## 5 STUDY PROCEDURE

**Transcendental Meditation (TM):** TM is an effortless technique that produces a state of ‘restful alertness’ associated with a more integrated style of brain functioning. TM will be delivered to participants by certified instructors of the program in a standardized format (see below; also Roth, 2018; Nidich et al., 2018; Schneider et al., 2012). The TM technique is not based on religious or other philosophical beliefs and does not involve major changes to one’s lifestyle. Important advantages of employing TM in research include a standardized and reproducible instruction format, a thorough certification program for instructors, and widespread availability of instructors in North America and in major cities throughout the world.

Two experienced certified TM instructors will conduct the instruction. All certified TM teachers have been extensively trained in the teaching of the TM program, including teaching the initial course of instruction, verifying continued correctness of effortless practice of the technique, and conducting additional follow-up sessions. The same standardized TM course sequence will be used for all study participants.

**Outline of Transcendental Meditation Program:** TM will involve 10 total sessions over 12 weeks. The core training in the TM technique will be done over five sessions. The five core instruction sessions will include: a) Introductory/Preparatory Lecture—review of previous scientific research on the TM program and a discussion of the mechanics and origin of the TM technique; b) Personal Instruction—individual one-on-one instruction in the TM technique (75 minutes); c) First Day of Verification of Correct Practice and Further Instruction (75 minutes-group session); d) Second Day of Verification of Correct Practice—understanding the mechanics of the TM technique from personal experiences (75 minutes-group session); e) Third Day of Verification of Correct Practice—understanding the mechanics of the development of higher human potential and wellness (75 minutes-group session).

Following the initial phase of the intervention (5 sessions), there will be 3 additional group sessions, each 45 minutes’ duration, provided once a month for the remainder of the 3-month intervention period. These sessions will include: a) discussion of personal experiences and verification of correctness of practice of the TM technique, and b) knowledge of the human potential and its relationship to mental and physical health.

Compliance with sessions will be defined as attending at least 70% of the treatment sessions.

**Home Practice:** Home practice will consist of two 20-minute TM sessions daily - morning and evening. Compliance with TM practice will be defined as meditating at least once a day. Participants will complete a home practice questionnaire at 1 month and 3 months. A Subject Diary will be used to record compliance.

**Lifestyle-As-Usual (LAU) Control Condition:** Subjects in the control group will continue with their usual lifestyle.

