## **7.2 Statistical Methods**

### **7.2.1 General Statistical Methods**

For all primary and secondary outcomes, data will be analyzed using analysis of covariance (ANCOVA). Dependent variable will be change from baseline at three-month post-test, with treatment group as the independent variable, and baseline dependent variable as the covariate. Missing data will be imputed using last observation carried forward (LOCF). Effect sizes will be calculated using Cohen's d: mean differences divided by pooled standard deviation. For the primary outcome, change in total burnout, the significance level will be set at  $p < .05$ , two-tailed. For all secondary outcomes,  $p < .01$ , two-tailed, will be used (to compensate for multiple comparisons).

The primary population for analyses of efficacy data will be ITT population. A supportive analysis will be presented for the PP population if this is significantly different from the ITT population. Continuous data will be summarized by using descriptive statistics (number, mean, median, standard deviation, minimum, and maximum).

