#### **7.2.2 Sample Size**

The total sample size needed is 130 subjects. 65 intervention and 65 matched control group

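### TM is taught mostly in groups but the fixed ANCOVA treats all participants as independent, so the 5% level and the confidence interval are not assured

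*Protocol*

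**What the plan says.** **Delivery (Protocol section 5).** "Two experienced certified TM instructors will conduct the instruction". Of the five core sessions, one is one-on-one and three are held in groups, the first of them being "First Day of Verification of Correct Practice and Further Instruction (75 minutes-group session"). The format of the introductory lecture is not given. After the core course "there will be 3 additional group sessions", one a month, in which participants talk through their own experiences. That makes 3 + 3 = 6 group sessions among the 5 + 3 = 8 itemised. The same section gives a total of 10 sessions; the two counts need to be reconciled before the group share is exact. Controls carry on as usual and are taught nothing.

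**Analysis (Protocol section 7.2.1).** "Dependent variable will be change from baseline at three-month post-test, with treatment group as the independent variable, and baseline dependent variable as the covariate". Total burnout is tested at 5% two-sided, the secondary outcomes at 1%.

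**Size (Protocol section 7.2.2).** "The total sample size needed is 130 subjects. 65 intervention and 65 matched control group". No effect size, SD, power, ICC or design effect is given.

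**Recruitment (Protocol section 3.2).** The TM arm is spread 25/25/15 over three hospitals. Similar numbers of controls come from each, matched as far as possible on gender, age, type of provider and work schedule.

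**The concern.** People taught together share an instructor, a group atmosphere and possibly a shift or unit, so their outcomes may be correlated. This grouping exists in the TM arm only: the design is partially nested. A two-term ANCOVA with independent errors ignores it. Positive within-group correlation makes the variance of the TM mean larger than the model assumes. Taken alone, that shortens the confidence interval for the treatment effect and lifts the error rate above the nominal level.

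There is also a practical risk. The protocol nowhere provides for recording who was taught in which group. If this is not captured during the trial, no later analysis plan can make use of it.

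**Working it through.** **Inputs from the protocol:** 65 per arm (7.2.2); two-sided 5% (7.2.1); hospitals 25/25/15 (3.2); group delivery in the TM arm only (5). **Not given, so assumed:** TM group size m = 5, 8 or 13 (13, about 8 or 5 groups); ICC ρ = 0.02, 0.05 or 0.10; residual variance shares s for hospital and p for matched pair. The total of 130 cannot be reproduced because no inputs are stated. Under independence, 65 per arm has 81% power for an assumed d = 0.5.

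**Step 1: TM clustering alone.** With residual variance σ², the TM mean has variance σ²[1 + (m − 1)ρ]/65 and the control mean σ²/65. The ANCOVA assumes 2σ²/65 for the difference. Hence

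true variance / assumed variance = 1 + (m − 1)ρ/2,

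true error = 2[1 − Φ(1.96/√ratio)].

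Example, m = 8 and ρ = 0.05: ratio = 1 + 7 × 0.05/2 = 1.175; √1.175 = 1.084; 1.96/1.084 = 1.81; error 7.1%.

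| m | ρ = 0.02 | ρ = 0.05 | ρ = 0.10 |
|---|---|---|---|
| 5 | 5.5% | 6.2% | 7.4% |
| 8 | 5.8% | 7.1% | 9.2% |
| 13 | 6.4% | 8.6% | 12.1% |

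The SE is understated by a factor of 1.02 (m = 5, ρ = 0.02) to 1.27 (m = 13, ρ = 0.10). Simulating the protocol's ANCOVA (10,000 runs per cell, groups formed within hospitals) gives 5.0% at m = 8 and ρ = 0, 6.8% at m = 8 and ρ = 0.05, 8.6% at m = 8 and ρ = 0.10, and 8.1% at m = 13 and ρ = 0.05. For the 1% tests at ρ = 0.05, the formula with 2.576 in place of 1.96 gives 1.8% (m = 8) and 2.4% (m = 13).

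**Step 2: add the shared hospitals and the matching.** Correlation shared between the arms cancels from the difference but stays in the ANCOVA residual, so it works the other way. Approximately,

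ratio = 1 − s − p + (m − 1)ρ/2,

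so the error exceeds 5% only when (m − 1)ρ/2 is larger than s + p.

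| m | ρ | s | p | ratio | error, formula | error, simulated ANCOVA |
|---|---|---|---|---|---|---|
| 8 | 0 | 0.05 | 0.10 | 0.850 | 3.4% | 3.5% |
| 8 | 0.05 | 0.05 | 0.10 | 1.025 | 5.3% | 5.4% |
| 8 | 0.05 | 0 | 0.20 | 0.975 | 4.7% | 4.6% |
| 13 | 0.05 | 0.05 | 0.10 | 1.150 | 6.8% | 6.8% |

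**Step 3: does a nested analysis work at this size?** This was checked with a simplified version, TM group means against individual controls with Satterthwaite degrees of freedom (6,000 runs), not with the full mixed model. Without hospital or matching correlation, at ρ = 0.05 and m = 5, 8, 13 it rejects 4.7%, 5.5% and 5.1%; at ρ = 0.10, 5.4%, 5.1% and 5.9%. With s = 0.05 and p = 0.10 but no hospital term it over-corrects, rejecting about 2.5% to 4%. With a hospital term added it rejects about 4% to 6.5% over the cases run, against about 4% to 13% for the independent-data test.

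**The case against.** The strongest reply is that nothing in the document shows the error rate to be wrong. ICC and group size are absent. Section 5 does not say that groups are fixed or that the monthly sessions keep the same members. If TM helps nobody, clustering caused by its delivery may be close to zero, although groups formed by shift or unit could still differ. The hospital and matching correlation that the same ANCOVA ignores pushes the other way and can cancel or reverse the inflation. All of this stands, and it limits the claim.

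A reader might go further and infer that the 5% level is definitely broken, or that the error favours TM. The documents support neither. The net direction depends on quantities they do not give. The tests are two-tailed, and an understated variance raises false rejections equally for and against TM; it creates no bias toward either arm. Nor can the two instructors be treated as random clusters: two levels are too few to estimate a variance.

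It can also be said that a separate statistical analysis plan, referred to in section 8.2, may handle this. But 7.2.1 itself fixes the outcome, the model terms and the significance level. A later plan also cannot recover group membership that was never recorded. Finally, an offset between two ignored correlations is not a safeguard, since the matching is only as close as recruitment allows.

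**Conclusion.** The point holds in limited form: the fixed analysis ignores a dependence that the design creates, so the nominal level and the interval are not assured. With no offset, groups of 5 to 13 and ICC 0.02 to 0.05, the true error is about 5.5% to 8.6%, and up to about 12% at ICC 0.10. With hospital and matching shares of 0.05 and 0.10 it ranges from about 3.5% (no TM clustering) to 6.8% (m = 13, ICC 0.05). Group sizes, ICCs and variance shares are all assumptions. The matter merits a change because the correction is cheap and depends on data that must be collected during the trial. Non-randomised allocation is a separate and probably larger threat to the comparison, and nothing here addresses it.

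**What to change.** 1. Record on the CRF the course group of each TM participant, and the instructor for description only.
2. In section 7.2.1, keep treatment and baseline, and add hospital as a fixed effect and the matching factors (gender, age, type of provider, work schedule) as covariates. Add a random effect for course group in the TM arm only, each control being its own unit. Use Satterthwaite or Kenward-Roger degrees of freedom.
3. Report the plain ANCOVA alongside.

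The hospital term is needed: without it, groups formed within hospitals absorb variation that both arms share, and the test becomes conservative.

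The cost is one or two CRF entries, a few lines of text and a somewhat wider interval. At an assumed d = 0.5 with no true clustering, power falls from about 81% to 80%, 79% or 75% with 13, 8 or 5 groups (calculated without hospital terms), so the loss is 1 to 6 points and largest with about five groups.
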